## Abstract

Background: Intraoperative hypotension is common in patients having non-cardiac surgery and associated with postoperative acute myocardial injury, acute kidney injury, and mortality. Avoiding intraoperative hypotension is a complex task for anesthesiologists. Using artificial intelligence to predict hypotension from clinical and hemodynamic data is an innovative and intriguing approach. The Acumen^TM^ Hypotension Prediction Index (HPI) software (Edwards Lifesciences; Irvine, CA, USA) was developed using artificial intelligence—specifically machine learning—and predicts hypotension from blood pressure waveform features. We aimed to describe the incidence, duration, severity, and causes of intraoperative hypotension when using HPI monitoring in patients having elective major non-cardiac surgery. Methods: We built up a European, multicenter, prospective, observational registry including at least 700 evaluable patients from five European countries. The registry includes consenting adults (≥18 years) who were scheduled for elective major non-cardiac surgery under general anesthesia that was expected to last at least 120 min and in whom arterial catheter placement and HPI monitoring was planned. The major objectives are to quantify and characterize intraoperative hypotension (defined as a mean arterial pressure [MAP] < 65 mmHg) when using HPI monitoring. This includes the time-weighted average (TWA) MAP < 65 mmHg, area under a MAP of 65 mmHg, the number of episodes of a MAP < 65 mmHg, the proportion of patients with at least one episode (1 min or more) of a MAP < 65 mmHg, and the absolute maximum decrease below a MAP of 65 mmHg. In addition, we will assess causes of intraoperative hypotension and investigate associations between intraoperative hypotension and postoperative outcomes. Discussion: There are only sparse data on the effect of using HPI monitoring on intraoperative hypotension in patients having elective major non-cardiac surgery. Therefore, we built up a European, multicenter, prospective, observational registry to describe the incidence, duration, severity, and causes of intraoperative hypotension when using HPI monitoring in patients having elective major non-cardiac surgery.

## 1. Introduction

Intraoperative hypotension—i.e., low arterial blood pressure during surgery—is common in patients having non-cardiac surgery with general anesthesia [1]. Intraoperative hypotension is associated with postoperative acute myocardial and kidney injury [2,3,4,5,6] and postoperative mortality [2,7,8,9]. Intraoperative hypotension is a potentially modifiable risk factor for postoperative morbidity and mortality and should be avoided [10,11].

Avoiding intraoperative hypotension is a complex task for anesthesiologists [12]. Current blood pressure management is mainly reactive—with fluids and vasopressors being given to treat hypotension when it has already occurred. However, hypotension is a late clinical sign of hemodynamic instability and exhausted compensatory mechanisms. Predicting hypotension before it becomes clinically apparent, therefore, may allow preemptive treatment and help avoid hypotension [13]. Using artificial intelligence to predict hypotension from hemodynamic data is an innovative and intriguing approach.

The Acumen^TM^ Hypotension Prediction Index (HPI) software (Edwards Lifesciences; Irvine, CA, USA) was developed using artificial intelligence—specifically machine learning—and predicts hypotension from blood pressure waveform features [14]. The HPI is a unitless number ranging from 0 to 100. It indicates the likelihood that a patient will develop hypotension, defined as a mean arterial pressure (MAP) of less than 65 mmHg for at least one minute. The higher the HPI, the higher the likelihood that hypotension will occur shortly. HPI values over 85 trigger acoustic and visual alarms, a pop-up window, and a “secondary screen”. The secondary screen displays advanced hemodynamic variables to support clinicians to diagnose the cause of impending hypotension and initiate causal treatment.

We aimed to investigate whether using HPI monitoring helps avoid intraoperative hypotension. We built up a European, multicenter, prospective, observational registry to describe the incidence, duration, severity, and causes of intraoperative hypotension when using HPI monitoring in patients having elective major non-cardiac surgery.

## 2. Materials and Methods

EU-HYPROTECT is a European, multicenter, prospective, observational registry in patients having elective major non-cardiac surgery. The registry was conducted in accordance with the recommendations guiding physicians in biomedical research involving human subjects adopted by the 18th World Medical Assembly, Helsinki, Finland, 1964 and later versions, and in accordance with the European Medical Device Regulation (Regulation (EU) 2017/745 of 5 April 2017), and ISO 14155:2020. Ethics committee approval was obtained for each site prior to patient documentation. Patients provided written informed consent before study inclusion (unless waived by the local ethics committee due to the observational nature of the study). The study was registered at ClinicalTrials.gov (NCT04972266) on 22 July 2021 (Table 1). This article adheres to the Standard Protocol Items: Recommendations for Interventional Trials (SPIRIT) statement [15]. The first patient was enrolled in this registry on 27th September 2021.

### 2.1. Participating Sites

We collected data from 12 medical centers in 5 European countries (France, Germany, Italy, Spain, and United Kingdom). All participating sites had experience performing clinical research with patient-centered outcomes, agreed to the feasibility of recruitment, had electronic medical records containing procedural perioperative data of surgical patients, and verified the ability to recruit patients. Written informed consent was obtained from patients by the research team.

Patients in the registry were monitored using an advanced hemodynamic monitoring system, the Acumen^TM^ IQ sensor (Edwards Lifesciences) and the Hemosphere platform (Edwards Lifesciences), which calculates and continuously displays the HPI. Because using the HPI requires training and education, the registry was performed in medical centers that routinely use HPI monitoring with the Acumen^TM^ IQ sensor and the Hemosphere platform.

### 2.2. Patients

We planned to include at least 700 evaluable patients in the registry. We included consenting adults (≥18 years) who were scheduled for elective major non-cardiac surgery under general anesthesia that was expected to last at least 120 min and in whom arterial catheter placement and HPI monitoring was planned for clinical indications. We did not include patients having emergency surgery, nephrectomy, and liver or kidney transplantation; patients with atrial fibrillation and/or sepsis (according to current Sepsis-3 definition); patients with American Society of Anesthesiology physical status classification V or VI; patients who were not able to understand the nature, significance, and scope of the investigation; pregnant women; patients without signed informed consent/data protection statement; and patients participating in interventional trials.

### 2.3. Objectives and Outcomes

Once all the data will be collated, the major objectives will be to quantify and characterize intraoperative hypotension (defined as a mean arterial pressure (MAP) < 65 mmHg) when using HPI monitoring in patients having elective major non-cardiac surgery. This threshold was chosen because evidence from observational research suggests that the population harm threshold for postoperative organ injury is 60–70 mmHg for MAP [16] and the HPI software is trained to predict a MAP of 65 mmHg for at least one minute. Specifically, we will describe the time-weighted average (TWA) MAP < 65 mmHg (unit: mmHg)—that is the area under a MAP of 65 mmHg (unit: mmHg × minutes) divided by the total monitoring time (i.e., usually the total duration of surgery) (unit: minutes) [17,18]. We will also describe the TWA MAP < 60 mmHg and <55 mmHg; the area under a MAP of 65 mmHg, 60 mmHg, and 55 mmHg; the number of episodes of a MAP < 65 mmHg, <60 mmHg, and <55 mmHg; the proportion of patients with at least one episode (1 min or more) of a MAP < 65 mmHg, <60 mmHg, and <55 mmHg; and the absolute maximum decrease below a MAP of 65 mmHg, 60 mmHg, and 55 mmHg. We will also assess the primary causes of intraoperative hypotension by analyzing advanced hemodynamic variables during hypotensive episodes (including cardiac output, stroke volume, heart rate, systemic vascular resistance, pulse pressure variation, stroke volume variation, dP/dt_max_, and dynamic arterial elastance). On an exploratory basis, we will describe the incidence of (1) postoperative acute myocardial injury within 3 days after surgery, (2) postoperative acute kidney injury within 3 and 7 days after surgery, (3) death within 30 days after surgery, 4) hospital re-admission within 30 days after surgery, and (5) a composite outcome of non-fatal cardiac arrest and death within 30 days after surgery. For this purpose, we follow patients for 30 days after surgery (via a phone call if the patient leaves hospital earlier than 30 days after surgery).

Acute myocardial injury was defined as an increase in high-sensitivity troponin concentration within the first three postoperative days according to the definition of “myocardial injury and infarction associated with non-cardiac procedures” set forth in the Fourth Universal Definition of Myocardial Infarction (2018) [19]. We considered high-sensitivity troponin T or I values (whichever was used in each center) when measured per routine care before surgery (baseline) and on postoperative days 1, 2, or 3.

Acute kidney injury was defined based on “Kidney Disease: Improving Global Outcomes Clinical Practice Guideline for Acute Kidney Injury” [20,21] as (a) an increase in serum creatinine concentration of ≥0.3 mg/dL within any 48-h period within the first 7 postoperative days, (b) an increase in serum creatinine of ≥50% from baseline within the first 7 postoperative days, or (c) the need for renal replacement therapy within the first 7 postoperative days. We considered serum creatinine values when measured per routine care before surgery (baseline) and on postoperative days 1 to 7. We only considered the creatine and renal replacement criteria (i.e., excluding the urine output criterium) in accordance with current recommendations [20,21] because urine output is usually not reliably recorded in patients after surgery.

Non-fatal cardiac arrest was defined as successful resuscitation from ventricular fibrillation, ventricular tachycardia, asystole, or pulseless electrical activity requiring cardiopulmonary resuscitation, pharmacological therapy, or cardiac defibrillation.

Further, we will describe the intensive care unit length of stay and hospital length of stay. It will be documented whether an institutional hemodynamic protocol was available.

We will compare the incidence, duration, and severity of intraoperative hypotension observed in patients in the present registry with those reported in previous observational and interventional studies using similar metrics quantifying intraoperative hypotension and reporting postoperative complications (“historical data” from studies published in international peer-reviewed journals).

We will also compare the incidence, duration, and severity of intraoperative hypotension observed in patients in the EU-HYPROTECT registry with those observed in patients in whom HPI monitoring was not used. Hemodynamic data from such patients are available to Edwards Lifesciences because they are being shared under the umbrella of different joint projects between Edwards Lifesciences and hospitals using Edwards Lifesciences monitoring (data share agreements are in place with all institutions sharing patient data).

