### 2.5. Statistics

The sample size was estimated based on published data. A randomized controlled trial reported a TWA MAP < 65 mmHg of 0.44 mmHg (25% and 75% percentiles, 0.23 and 0.72 mmHg) without and 0.10 mmHg (25% and 75% percentiles, 0.01 and 0.43 mmHg) with HPI monitoring [18]. Considering the wide interquartile range of TWA MAP < 65 mmHg, we planned to include at least 700 evaluable patients in this registry.

Statistical analysis will be performed for the total registry population, as well as for subgroups. We will perform descriptive analyses to describe and quantify intraoperative hypotension, patient characteristics, and perioperative data. For continuous variables, means with standard deviations will be presented for normally distributed data and medians with 25th and 75th percentiles for non-normally distributed data. For categorical variables, numbers and percentages will be shown. Patients with missing data will be excluded from the analysis. All statistical analyses will be performed using IBM SPSS Statistics (IBM, Armonk, NY, USA) or R Core Team (Version 4.2.1; R Core Team/R Foundation for Statistical Computing, Vienna, Austria; https://www.R-project.org/; date accessed: 19 September 2022).

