The HPI algorithm was developed by Hatib and co-workers [14] for the real-time prediction of hypotension. The HPI algorithm was modeled and cross-validated in 1334 surgical and critically ill patients using 545,959 min of arterial blood pressure waveform recordings and 25,461 episodes of hypotension [14]. It was externally validated in 204 surgical patients [14]. The HPI predicts hypotension—in the current version defined as a MAP < 65 mmHg for at least 1 min—from 23 individual arterial blood pressure waveform features (that were identified from 3022 individual and 2,606,147 combinatorial waveform features) [14].

Validation studies in surgical patients suggest that the HPI may predict hypotension 15 min before the event with a sensitivity and specificity of more than 80% [14,26]. HPI-guided blood pressure management reduced intraoperative hypotension compared to routine care in small preliminary trials in patients having hip arthroplasty [27] and general non-cardiac surgery—but not in a trial randomizing 212 non-cardiac surgery patients to HPI-guided or routine blood pressure management [28].

We included consenting adults having elective major non-cardiac surgery with general anesthesia in whom arterial catheter placement and HPI monitoring was planned for clinical indications independent of the study. We used duration of surgery (at least 120 min) to select patients having major surgery who are at particular risk of developing hypotension. Although the HPI algorithm also works on blood pressure waveforms recorded non-invasively using a finger-cuff device [29,30], we only included patients in whom blood pressure is monitored invasively using an arterial catheter because intraarterial blood pressure monitoring remains the clinical reference method [31]. Patients having emergency surgery were not included because these patients would not have enough time to provide informed consent. Patients with atrial fibrillation were not included because the HPI algorithm is not validated in patients with atrial fibrillation. Sepsis causes marked alterations in cardiovascular dynamics—including alterations in vasomotor tone and blood pressure regulation. We, therefore, also excluded septic patients from the registry.

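### The Introduction sets an effectiveness aim that a registry without a non-HPI group cannot answer, and the two external comparisons are not labelled non-causal

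*Protocol article*

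**What the plan says.** **Aim.** The Introduction says: "We aimed to investigate whether using HPI monitoring helps avoid intraoperative hypotension". Its next sentence, like the abstract, only describes incidence, duration, severity and causes. Section 2.3 agrees with the descriptive version: "the major objectives will be to quantify and characterize intraoperative hypotension".

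**Design.** "EU-HYPROTECT is a European, multicenter, prospective, observational registry in patients having elective major non-cardiac surgery". Section 2.1 adds that all registry patients were monitored with HPI, at centres that use it routinely.

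**Comparisons.** Section 2.3 plans two. The first sets the registry results alongside "with those reported in previous observational and interventional studies using similar metrics quantifying intraoperative hypotension"; these studies must also report postoperative complications and be published in international peer-reviewed journals. The second compares hypotension "with those observed in patients in whom HPI monitoring was not used. Hemodynamic data from such patients are available to Edwards Lifesciences", the stated reason for availability being that "they are being shared under the umbrella of different joint projects between Edwards Lifesciences and hospitals using Edwards Lifesciences monitoring".

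**Analysis.** Section 2.5: "We will perform descriptive analyses to describe and quantify intraoperative hypotension, patient characteristics, and perioperative data".

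**The concern.** Whether monitoring helps avoid hypotension is a question about a contrast: what would have happened to these patients without it. The registry contains no patient who could supply that contrast. Any answer must come from the two external sources, and the article does not say that those sources have to resemble the registry population.

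The sponsor makes the device and holds the non-HPI recordings. If the registry shows less hypotension than the comparator, the Introduction's aim (and the scientific title in Table 1, which speaks of preventing hypotension) invites the reader to credit the device. If it shows more, the reader may wrongly conclude that the device fails. Nothing in the article warns against either inference.

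**Working it through.** **Step 1: aim against design.**

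| Place in the protocol article | Type of statement |
|---|---|
| Introduction, aim sentence | Effect of HPI monitoring |
| Introduction, next sentence; abstract | Descriptive |
| Section 2.1 | All patients HPI-monitored; no internal control |
| Section 2.3, major objectives | Descriptive |
| Section 2.3, last two comparisons | External contrasts |
| Section 2.5 | Descriptive analyses |
| Table 1, key outcomes | Descriptive; no contrast with non-HPI patients |

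One sentence asks an effect question, and only the two external contrasts could address it.

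**Step 2: what could differ between the sources.**
- *Case mix.* Section 2.2 excludes, among others, emergency surgery, atrial fibrillation and sepsis, and requires an expected duration of at least 120 min. The Discussion gives reasons: sepsis changes vasomotor tone and pressure regulation, and long surgery selects patients prone to hypotension. A comparator without the first restriction could show more hypotension than the registry. On the plan's own reasoning, one without the second could show less. The direction is therefore open.
- *Centre and indication.* Sites were those that routinely use HPI, and HPI was planned for clinical indications, so exposure is tied to both.
- *Metric.* Section 2.3 divides the area under 65 mmHg by total monitoring time, usually the duration of surgery. The Discussion divides by duration of surgery. A different denominator in the comparator would shift TWA by itself. Area and number of episodes also accumulate with time.

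**Step 3: how little bias would matter (illustration).** Section 2.5 gives TWA medians of 0.44 mmHg (quartiles 0.23, 0.72) without HPI and 0.10 mmHg (0.01, 0.43) with HPI, a difference of 0.34. It gives no error rate, power or precision target, so the figure of 700 cannot be reproduced; that is not the issue here.
- Rough SD = interquartile range / 1.349: 0.49/1.349 = 0.363 and 0.42/1.349 = 0.311. Pooled: √[(0.363² + 0.311²)/2] = 0.338.
- Assume 700 comparator patients and no HPI effect. SE = 0.338 × √(1/700 + 1/700) = 0.0181. A shift of 1.96 × 0.0181 = 0.035 mmHg would reach nominal significance, and 0.035/0.34 is about 10% of the cited difference.
- With 350 to 5,000 comparator patients the shift is 0.043 to 0.027 mmHg, or 13% to 8%.

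This uses a normal approximation to skewed data and a test that the article does not plan. It shows only that random error is small at this sample size, so bias would dominate.

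**Step 4: bias in either direction (assumed inputs).** Let a fraction f of comparator patients be of types that the registry excludes, with k times the mean TWA. With no HPI effect, the registry mean appears lower by 1 − 1/(1 − f + fk).
- f = 0.2, k = 2: 1 − 1/1.2 = 16.7% lower. f = 0.2, k = 3: 1 − 1/1.4 = 28.6% lower.
- f = 0.1, k = 1.5: 4.8% lower. f = 0.3, k = 3: 37.5% lower.
- f = 0.2, k = 0.5: 1 − 1/0.9 = −11.1%, that is, 11.1% *higher*.

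On medians the figures change. With a lognormal fitted to 0.44 (0.23, 0.72), the first two cases give about 12% and 17%. No value of f or k comes from the documents, so none of these figures is an estimate.

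**The case against.** **The effect sentence is isolated.** Every other statement of purpose is descriptive. The Discussion says a randomized trial would have been desirable, that power is insufficient for patient-centred outcomes, and that the results will inform future trials. This is fair, and it limits the severity. But those remarks concern power and future designs. They do not say that the hypotension contrasts are confounded or non-causal.

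**Selection and adjustment belong in the analysis plan.** This stands. A reader might infer that the comparison is crude and unmatched, or takes in every shared recording. The article does not say so; it names a source and is silent on selection. Nor does it say that hemodynamic data are the only data held, so a lack of covariates cannot be assumed.

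**The historical contrast is not open-ended.** Also correct. Studies must report complications and be peer-reviewed, and the article does not say when they are chosen. A reader might think that the plan rests on two conflicting benchmark trials, but section 2.5 uses one. The other appears in the Discussion, where the authors themselves report that HPI reduced hypotension in small trials "but not in a trial randomizing 212 non-cardiac surgery patients to HPI-guided or routine blood pressure management". What remains is that the mixed evidence makes the choice of studies matter.

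**Different processing is unproven.** The comparator hospitals use the same manufacturer's monitoring. True, but the time window and denominator still need to be the same.

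**Conclusion.** The mismatch is real and lies in the article's own text: an effect aim, no internal non-HPI group, descriptive analysis, and external contrasts without a non-causal label or a stated link to the registry's eligibility. No analysis plan can turn this design into one that answers the Introduction's question, though it may reduce bias in the contrasts.

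The size and direction of any bias cannot be estimated from the documents. The figures in steps 3 and 4 rest on an assumed comparator size, assumed case mix and an approximate SD. They do not support a statement that the registry will show a particular spurious reduction. Nor do the documents support saying that the authors intend to attribute a difference to HPI; that is an inference the wording permits, not one it makes.

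This should be fixed. The descriptive objectives, which are the registry's main purpose, stand as they are.

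**What to change.** 1. **Aim.** Replace the effect sentence in the Introduction with the descriptive aim of the abstract. State that both comparisons in section 2.3 are exploratory and support no claim of an HPI effect.
2. **Non-HPI recordings, if kept.** Restrict them to patients who meet the section 2.2 criteria (other than HPI use) as far as the shared data allow. Compute TWA with one time window and one denominator in both sources. Adjust for case mix where covariates exist; otherwise show the results side by side without attribution. The adjustment method and covariate list can be left to the analysis plan.
3. **Historical data.** Include HPI trials with positive and with negative results.

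**Cost.** Wording, plus analysis work on data already held. Recruitment and follow-up are complete, so no patient or visit is affected. The downside is a smaller comparator set and a weaker claim.
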